### 2.1. Study Population

Participants will be recruited from Warsaw’s primary schools and primary health-care units according to the inclusion criteria: (i) symptoms of post-COVID-19 condition lasting more than one month following initial COVID-19 infection confirmed by the diagnosis by general practitioner (including obligatory fatigue and shortness of breath/respiratory problems); (ii) age 10–12 years old. As it has been suggested that a positive COVID-19 test is not required for a diagnosis of post-COVID-19 condition [27], there will be an optional inclusion criteria: positive RT-PCR test and/or positive result in test for antibodies against the SARS-CoV-2 coronavirus 1–8 months prior to the study start. The exclusion criteria will consist of: absolute contraindications to exercise; unstable cardiac conditions; currently engaged in regular exercise training more than twice per week. The necessary minimum total number of participants (n = 84) was obtained using the G*Power program assuming detection of a moderate effect size of REPETITIONxGROUP interaction (d = 0.50 or eta square 0.06) for exercise capacity and fatigue with a significance level of 0.05 and statistical power of 0.85.

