### 2.2. Randomization

Participants meeting the inclusion criteria will be randomized to one of 3 groups: water-based exercise, land-based exercise, or control (no exercise). The randomization sequence will be designed by an investigator external to the study using an Excel random number generator. Group allocation will be prepared in 5 random versions. Finally, the allocation providing the lowest F value for MANOVA comparing basic characteristics of the study subjects will be used. Randomization will be stratified according to age, sex, and the level of exercise capacity. Concealed allocation will be achieved using opaque envelopes. Due to the nature of exercise interventions, it will not be possible to blind the physiotherapist or participants. 

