### 2.3. Outcome Measures

Outcome measures will be collected at baseline and immediately after the 8-week intervention. Table 1 shows the distribution of the different measures across the time points during the study (SPIRIT table).

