### 2.6. Statistical Analysis

Normality of the distributions of the quantitative variables under study will be tested using the Shapiro–Wilk test. Data will be presented as mean ± SD where appropriate. The mixed-design ANOVA will be used to compare means. The interaction of fixed and repeated factors will be analyzed. Tukey’s post hoc test will be used for detailed comparisons. For variables that do not meet the criteria of normality of distribution, data will be presented as medians and quartile range. The Mann–Whitney U test will be used to compare the groups. The variables as well as their increments will be analyzed. Effect sizes will be assessed by partial eta squared (ANOVA) or the Glass rank-biserial correlation coefficient (the Mann–Whitney U test). The agreement of children’s and parents’ responses in the PedsQLTM 4.0 questionnaire will be analyzed with the compatibility factor Kappa-k. All statistical calculations will be conducted using the Statistica 14.0.0.15 program (TIBCO Software Inc., Palo Alto, CA, USA, 2020).

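### With exactly three arms, a closed test would give more power than Tukey for each programme versus control, at the same 5% familywise error per outcome: an inexpensive improvement, not an error

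*Protocol article*

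**What the plan says.** Section 2.2 fixes the number of arms: children are "randomized to one of 3 groups: water-based exercise, land-based exercise, or control (no exercise"). Section 2.3 fixes two measurement times: "Outcome measures will be collected at baseline and immediately after the 8-week intervention". Section 2.6 specifies a mixed-design ANOVA and says "The interaction of fixed and repeated factors will be analyzed", then that Tukey's "post hoc test will be used for detailed comparisons". It adds that increments are analysed as well as the variables themselves.

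Section 2.1 sizes the trial (n = 84) for the interaction alone, at a "significance level of 0.05 and statistical power of 0.85". It gives no power for a comparison of either programme with control. The Objectives section puts the effectiveness of the land and water programmes first, for exercise capacity and fatigue.

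**The concern.** A significant interaction shows only that the three arms do not all change alike. Whether the water or the land programme works is settled by the pairwise comparisons that follow. Tukey's test for three means holds each pair to about 0.019 instead of 0.05. If three arms allow the full 0.05 per pair after an omnibus test without exceeding 5% overall, the planned method gives up power at the step that answers the primary aim. An effective programme, or the second of two, is then more likely to be reported as not shown.

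**Working it through.** **The plan's own figure.** Section 2.1 gives n = 84 for "d = 0.50 or eta square 0.06) for exercise capacity and fatigue". For 3 groups and 2 times, the interaction test has noncentrality λ = f²·N·2/(1−ρ) with 2 and N−3 df, where ρ is the pre-post correlation. The article does not state ρ. With f = 0.25, ρ = 0.08 to 0.10 gives N = 82 to 84; ρ = 0.5 gives 46 to 47. So 84 can be reached but not confirmed from the stated inputs. The comparison below therefore fixes the effect directly on the scale of the change.

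**Inputs.** Three arms (section 2.2). Two times (section 2.3), so the interaction test equals a one-way ANOVA on the change. N = 84, alpha 0.05, power 0.85 (section 2.1). Up to 10% missing, complete cases (section 2.7): 84 × 0.9 = 75.6, about 25 per arm. Assumed: 28 per arm (84/3; the allocation ratio is not stated), normal changes and equal SDs.

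**Why the closed test keeps 5%.** Any two pairwise nulls together imply that all three arms are equal. Only two situations can therefore produce a false claim:
- All arms equal: a claim needs the omnibus test to reject, which has probability 0.05.
- Exactly one pair equal: only that pair can be falsely claimed, and it is tested at 0.05.

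**Critical values, 81 df.** Tukey: |t| > 2.388, a per-pair level of about 0.019. Unadjusted: |t| > 1.990. With the same omnibus gate, whatever Tukey rejects the closed test also rejects.

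**Effects.** If both programmes are better than control by d SDs of the change, λ = N·(2/9)·d².
- d = 0.785: λ = 84 × 0.2222 × 0.616 = 11.5, omnibus power about 0.855.
- d = 0.536: if eta squared 0.06 is partial on the change, f² = 0.06/0.94 = 0.0638 and d = √(0.0638 × 9/2) = 0.536, omnibus power 0.52.

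**Simulated power (at least 100,000 runs per scenario), omnibus + Tukey → closed test.**

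| Per arm | Differences from control (SD of change) | Each programme vs control | Both shown |
|---|---|---|---|
| 28 | 0.785 and 0.785 | 0.70 → 0.79 | 0.57 → 0.72 |
| 25 | 0.785 and 0.785 | 0.64 → 0.73 | 0.50 → 0.66 |
| 28 | 0.536 and 0.536 | 0.35 → 0.43 | 0.20 → 0.34 |
| 28 | 1.061 and 1.061 | 0.94 → 0.97 | 0.90 → 0.95 |
| 28 | 0.779 and 0 | 0.70 → 0.78 (the effective one) | not applicable |
| 28 | 0.45 and 0.90 | 0.25 → 0.38 and 0.82 → 0.84 | 0.24 → 0.37 |

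Power to show at least one programme in the first row is 2 × each − both: 2 × 0.705 − 0.569 = 0.84 with Tukey, and 2 × 0.788 − 0.720 = 0.86 with the closed test.

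**Familywise error for one outcome.** Closed test: 0.050 with all arms equal and 0.050 with one arm different. Omnibus + Tukey: 0.045 and 0.019.

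**Equivalent sample size.** For Tukey to reach 0.79 per programme: n = 2 × ((2.39 + 0.80)/0.785)² = 33 per arm, that is 99 children, and 99/84 = 1.18.

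**If Tukey is not gated.** At 0.785 SD, Tukey alone gives 0.71 per programme and 0.57 for both, so the gain from the closed test is nearly the same. Tukey alone does reject a pair that the F-gated closed test misses in about 0.7% to 1.5% of runs at these effects. With the three-group studentized range test as the gate, that no longer happens: any Tukey rejection implies a significant range, and |t| > 2.388 exceeds 1.990. At 0.779 SD this version gives 0.77 per programme and 0.70 for both, against 0.70 and 0.56 for Tukey alone.

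**The case against.** Tukey after a mixed ANOVA is valid and standard, and the article does nothing wrong in choosing it. That stands: the point is a gain in power, not a correction of an error.

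Four stronger readings are tempting, and the document does not support them.

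- *The pairs are protected twice.* Section 2.6 does not say that Tukey is used only after a significant interaction. The order of the sentences and the term post hoc suggest it, no more. The gate itself costs little (0.70 against 0.71 per programme); the loss comes from Tukey's critical value.
- *The closed test gives nothing up.* It gives up Tukey's simultaneous intervals. With one arm different, the error on the remaining true-null pair rises from about 0.019 to 0.05. That is within the 5% allowed, but the unused margin is spent.
- *Error is held at 5% for the trial.* It is held per outcome. There are two primary outcomes, and section 2.6 states no adjustment across them. If they were independent, with one arm different on both, the chance of at least one false pairwise claim would be 1 − 0.981² = 3.8% with Tukey and 1 − 0.95² = 9.8% with the closed test.
- *The trial will miss that exercise works.* If both programmes work, power to show at least one barely changes. The gain lies in showing the second programme, or the only effective one.

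It can also be said that section 2.6 does not name the family Tukey covers. If the detailed comparisons are the six group-by-time cell means, the figures above do not describe the plan and the shortcut does not apply to that family. The argument concerns the three between-arm differences in change, which are the contrasts that answer the aim.

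**Conclusion.** The point holds as an inexpensive improvement. For three between-arm differences in change, the closed test keeps 5% strong familywise control per outcome and raises power. At 28 per arm and 0.785 SD the gain is about 8 points for each effective programme versus control and about 15 points for showing both. The direction does not depend on the assumed effects when Tukey is gated by the omnibus test, or when the range test serves as the gate. The size does: from 3 points per programme at 1.061 SD to 13 points for the weaker programme under graded effects. The article gives no SD of change, so 0.785 SD is only the difference at which the interaction test has about the planned power. At 0.536 SD, omnibus power is 0.52 and no choice of pairwise test rescues the trial.

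**What to change.** In section 2.6, replace the Tukey sentence, as it concerns the interaction, with:

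> For each outcome analysed by ANOVA, if the group-by-time interaction is significant at 0.05, the three pairwise differences in change (water-control, land-control, water-land) are each tested at 0.05 with the pooled error term and no further correction (closed testing, three arms). If it is not significant, no pairwise claim is made. Individual (not simultaneous) 95% confidence intervals are reported and labelled as such.

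If Tukey was meant to run without an omnibus gate, use the three-group studentized range test as the gate, so that nothing Tukey would reject is lost.

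The cost is a few lines of text, with no extra data or children. The rule does not extend to the six cell means or to more than three arms. It leaves the Mann–Whitney branch unchanged (a Kruskal–Wallis gate would be the counterpart there), and it does not settle multiplicity across exercise capacity and fatigue.

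### For outcomes that fail the normality test, the plan compares three arms with a two-sample test on both values and increments, with no omnibus test, correction or deciding quantity

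*Protocol article*

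**What the plan says.** Section 2.2 sets the number of arms: "Participants meeting the inclusion criteria will be randomized to one of 3 groups" (water-based exercise, land-based exercise, no exercise). Section 2.3 has two assessments, at baseline and straight after the 8-week programme.

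Section 2.6 makes the analysis depend on a preliminary test: "Normality of the distributions of the quantitative variables under study will be tested using the Shapiro–Wilk test". Two branches follow.

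- **Normality criterion met:** mixed-design ANOVA, analysis of the group-by-repetition interaction, and Tukey's procedure for the detailed comparisons.
- **Normality criterion not met:** medians and quartiles as summaries, and then "The Mann–Whitney U test will be used to compare the groups".

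The next sentence reads "The variables as well as their increments will be analyzed". The effect-size sentence pairs partial eta squared with ANOVA and the rank-biserial coefficient with Mann–Whitney, so Mann–Whitney is the intended inferential test of the second branch.

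The only error rate in the document stands with the sample size in section 2.1, "with a significance level of 0.05 and statistical power of 0.85", for the repetition-by-group interaction in exercise capacity and fatigue, the two primary outcomes.

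**The concern.** A two-sample test cannot compare three arms in one step. Followed literally, the rank branch produces up to three pairwise p-values per quantity. With two quantities (value and increment) that is up to six per outcome. Tukey is a comparison of means and is named only beside the ANOVA. Nothing in the rank branch protects the pairwise tests, and nothing says whether a significant value, a significant increment, or either one, is the result.

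Exercise capacity and fatigue are the primary outcomes, and either could enter this branch. A positive finding from it could not be read at the 5% level. One primary outcome might also be judged with protected pairwise comparisons and the other without, depending on a preliminary test of the trial's own data.

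**Working it through.** **Inputs from the document.** Three arms (section 2.2); two assessments (section 2.3); significance level 0.05 and minimum total N of 84 (section 2.1); Mann–Whitney on values and increments (section 2.6).

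**Assumptions, not in the document.** Equal allocation, 84 / 3 = 28 per arm; two-sided tests; post-intervention scores taken as the values; pre–post correlation ρ varied from 0.3 to 0.9 because none is given.

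**The plan's own figure.** N = 84 was obtained for the interaction. With noncentrality λ = f²·N·m/(1 − ρ), m = 2, df = 2 and N − 3, and f = 0.25:

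- ρ = 0.08: λ = 0.0625 × 84 × 2 / 0.92 = 11.41, power 0.852. N = 84 is reproduced.
- ρ = 0: λ = 10.5, power at 84 is 0.820; the required N is 93.
- ρ = 0.5: λ = 21.0, power at 84 is 0.986; the required N is 48.

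So 84 is reached only with an assumed correlation of about 0.08–0.10. The present point does not depend on this. It matters only that the trial was sized on one interaction test at 0.05.

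**Number of tests.** Three arms give 3 × 2 / 2 = 3 pairs. Two quantities give 3 × 2 = 6 tests per outcome.

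**Reference values if the tests were independent**, 1 − 0.95^k:

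- k = 2: 1 − 0.9025 = 9.75%
- k = 3: 1 − 0.8574 = 14.3%
- k = 6: 1 − 0.7351 = 26.5%

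The tests share arms, and values and increments are correlated, so the true rates are lower.

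**Simulation with no true effect** (40,000 trials per setting, 28 per arm, Mann–Whitney at 0.05; normal, lognormal and bounded integer 0–60 scores). Chance of at least one p < 0.05 for one outcome:

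| Reading of the text | Rate |
|---|---|
| One Mann–Whitney test | about 5% |
| Two exercise-versus-control contrasts, post values | 8.8–9.3% |
| Three pairs, post values only | 11.9–12.5% |
| Three pairs, increments only | 12.0–12.4% |
| Two contrasts, values and increments | 15.5–17.0% |
| Three pairs, values and increments | 20.5–22.6% |

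Rates barely change with the correlation or the distribution. A continuity correction in the normal approximation lowers them slightly (for normal scores: 8.6–8.9% for two contrasts on one quantity, 11.6–12.0% for three pairs on one quantity, 20.3–21.7% for six tests). A further run of the same layout gave 11–12% and 19–22%. Rounded, the three main readings are about 9%, about 12% and about 19–22%.

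**After the repair, on increments.** A Kruskal–Wallis gate followed by pairwise tests gives 4.5–5.0%. The first step of Holm over three pairs (smallest p below 0.05/3) gives 4.0–4.3%.

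**Do increments answer the question the trial was sized on?** With two time points the interaction F in the mixed ANOVA equals the one-way F on the change score. On a simulated data set of 3 × 28 both were 1.664.

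**The case against.** **The rate is conditional and depends on the reading.** This stands. The article nowhere says that the tests are uncorrected; it names no correction in this branch. The stated aims concern the effectiveness of each exercise form, and water versus land is not listed as an aim, so two contrasts may be all that is meant. Saying that both quantities will be analysed is not the same as saying that either one can carry the claim. A flat statement that the false-positive rate is 20% would therefore go too far: the text supports a range of about 9% to 22%. The sentence on values and increments is also not clearly confined to the rank branch, so the double analysis may burden the ANOVA branch too.

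**A fuller plan may settle it.** An unseen analysis plan could add a correction. But the article does not leave the test open. It names one that does not fit three arms, so the fuller plan would have to change the stated method and not merely fill it in.

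**Stronger readings that the document does not support.**

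- *The rank branch gives up the group-by-time question.* It does not. With two assessments, comparing increments is that question, and increments are analysed. The fault is that values stand beside them with no order of priority.
- *A real treatment effect pushes an outcome into this branch.* With 84 pooled normal values and both exercise arms shifted, Shapiro–Wilk rejects in about 5% of trials with no shift, at 0.5 SD (the planned d) and at 1.0 SD. It reaches only about 7% at 1.5 SD.
- *Obligatory fatigue at entry truncates the fatigue score.* Section 2.1 requires fatigue as a symptom confirmed by a general practitioner. It sets no CFSQ threshold.
- *The rates can be compounded over both primary outcomes.* That would require both to enter the branch and to be independent, although they are measured in the same children. The document supports neither.

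**Conclusion.** The concern holds in a limited form and should be fixed. For an outcome that fails Shapiro–Wilk, section 2.6 prescribes a two-sample test for a three-arm comparison, on two quantities, with no overall test, no correction and no rule for which quantity decides. Followed as written, the chance of at least one false positive for that outcome is about 9% (two contrasts, one quantity), about 12% (three pairs, one quantity) or about 19–22% (three pairs, both quantities), against the stated 5%.

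The figures assume 28 children per arm, two-sided tests, no adjustment beyond what the article states and, for the highest range, that a significant value or a significant increment would each count as success. They apply only if the outcome enters the rank branch; the ANOVA branch has its interaction test and Tukey. A reader might infer that the primary analysis has to be replaced by a different model. The defect does not require that, because correcting the rank branch cures it.

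**What to change.** In the non-normal branch of section 2.6:

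1. Name the increment (post minus baseline) as the deciding quantity. With two time points it addresses the group-by-time question on which the trial was sized.
2. Test it across the three arms with Kruskal–Wallis at 0.05.
3. Run pairwise Mann–Whitney tests at 0.05 only if that test is significant. With three arms this sequence also protects the pairs: if one arm truly differs from the other two, only one true null pair is left. Alternatively, omit the gate and apply Holm over the three pairs.
4. Report post-intervention values descriptively, without a test that could carry the claim.

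The cost is a few sentences and no new data. Rank-based p-values become slightly less favourable, and an isolated pairwise result below 0.05 would no longer be enough on its own.

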#### 2.3.5. Health-Related Quality of Life

Health-related quality of life (HRQOL) will be measured with the Polish version of the Pediatric Quality of Life Inventory 4.0 Generic Core Scales (PedsQL^TM^ 4.0) for children and for parents. The Polish version of PedsQL^TM^ 4.0 was validated by Talarska et al. [36]. PedsQL^TM^ 4.0 is a brief, standardized, generic assessment instrument that systematically assesses perception of HRQOL in healthy children and those with acute and chronic health conditions. It is based on a modular approach to measuring HRQOL. The questionnaire contains 23 questions divided into the following subsections: physical functioning (8 items), emotional functioning (5 items), social functioning (5 items), and school functioning (5 items). The sum of these areas is the overall quality of life (total score). The responses are reported on a 5-point Likert scale ranging from 0 (no problem) to 4 (almost always), with a total score ranging from 0 (best HRQOL) to 100 (worst HRQOL) [37]. Further, two summarized functional children’s areas will be reported: the Physical Health Summary Score covering the area of Physical Functioning, and the Psychosocial Health Summary Score will be taken into account for analysis. Both participants and their parents will complete the questionnaire separately. It is planned to compare children’s and parents’ perception of the HRQOL of the child with post-COVID-19 condition. 

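### Child–parent agreement on PedsQL rests on kappa with no weights named, although the responses are ordered 0–4; read as ordinary kappa it understates item agreement

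*Protocol article*

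**What the plan says.** Section 2.6 (Statistical Analysis) gives one sentence to this analysis. Its subject is "The agreement of children’s and parents’ responses in the PedsQLTM 4.0 questionnaire", which "will be analyzed with the compatibility factor Kappa-k". It mentions no weighting scheme and no other agreement measure. It also does not say whether the unit is the single item, a subscale or a score.

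Section 2.3.5 (Health-Related Quality of Life) describes the data. On the items: "The questionnaire contains 23 questions divided into the following subsections" (8, 5, 5 and 5 items), and "The responses are reported on a 5-point Likert scale ranging from 0 (no problem) to 4 (almost always". It also describes a total score running from 0 to 100, and Physical and Psychosocial summary scores that enter the analysis. Child and parent each complete the form separately. The stated purpose is to "compare children’s and parents’ perception of the HRQOL" of the child.

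**The concern.** Cohen's kappa without weights is a measure for unordered categories. It credits exact matches and treats every mismatch alike. On an ordered 0–4 scale, a child answering 1 and a parent answering 2 count as being as discordant as a child answering 0 and a parent answering 4. Child and parent reports that sit mostly one step apart would therefore look weakly related.

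The second gap is that the planned comparison of perceptions naturally asks whether parents see the child's quality of life as better or worse than the child does, and by how much. Kappa, weighted or not, is a single coefficient and answers neither question. The mean comparisons in section 2.6 are framed by group and repeated measurement; no paired child–parent difference is named.

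At stake is how the child–parent comparison reads in the results paper. No treatment comparison depends on it.

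**Working it through.** The article states no figure for this analysis, so there is none to reproduce. The check is what kappa returns on data of the described kind.

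**Inputs from the article.** Five ordered response categories, 0–4; 23 items; total score 0–100 (section 2.3.5); 84 participants, hence 84 pairs (section 2.1).

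**Assumptions not in the article.** Child and parent ratings are bivariate normal with correlation r and no systematic shift. Item categories are cut at cumulative 25/50/75/92%. The total score has mean 65 and SD 15 on a grid of 23 × 4 + 1 = 93 values. A 5-item subscale has mean 65 and SD 20 on 5 × 4 + 1 = 21 values. Averages are over 400 simulated samples.

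**Formula.** κ = 1 − Σ w_ij p_ij / Σ w_ij p_i. p_.j, with w_ij = 1 for every i ≠ j (unweighted), |i − j| (linear) or (i − j)² (quadratic).

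**Step 1: a hand example.** Take five equally used categories and 50% mismatches.
- Chance agreement is 5 × 0.2² = 0.20, so unweighted κ = (0.50 − 0.20)/(1 − 0.20) = 0.375, whatever the size of the mismatches.
- The chance-expected squared difference is 2 × 2 = 4 (twice the variance of a uniform 0–4 variable).
- If every mismatch is one step, quadratic κ = 1 − (0.5 × 1)/4 = 0.875.
- If mismatches are spread evenly over the other categories, their mean squared size is 4/0.8 = 5, and quadratic κ = 1 − (0.5 × 5)/4 = 0.375.

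Unweighted kappa cannot tell these two situations apart.

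**Step 2: single items, 84 pairs.**

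| r | unweighted | linear | quadratic |
|---|---|---|---|
| 0.7 | 0.26 | 0.47 | 0.64 |
| 0.8 | 0.34 | 0.57 | 0.74 |
| 0.9 | 0.48 | 0.69 | 0.84 |

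Sensitivity to the cut-points: across three assumed sets at r = 0.7, unweighted kappa was 0.25–0.30, linear 0.46–0.47 and quadratic 0.61–0.65. The decimals move; the ordering does not.

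**Step 3: scores, only if kappa were applied to them.**

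| r | total: unweighted κ | total: exact matches | total: ICC | 5-item subscale: unweighted κ | subscale: ICC |
|---|---|---|---|---|---|
| 0.7 | 0.02 | 4% | 0.70 | 0.08 | 0.69 |
| 0.8 | 0.03 | 5% | 0.80 | 0.11 | 0.79 |
| 0.9 | 0.05 | 7% | 0.90 | 0.18 | 0.89 |
| 0.95 | 0.08 | 10% | 0.95 | 0.27 | 0.94 |

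With 93 possible values, exact matches are rare however close the pairs are, so unweighted kappa stays near zero while the ICC follows r.

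**The case against.** The strongest reply has four parts.

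- **Unit of analysis.** Section 2.3.5 uses the word responses for the item answers and speaks separately of total and summary scores. Section 2.6 applies kappa to responses. A reader might infer that kappa will be computed on the 0–100 scores and will collapse to nearly nothing. The text does not say so, and its own usage points to items. This part stands, and Step 3 is therefore conditional.
- **Weights.** The article neither states nor excludes them, and a condensed article may leave that detail to a fuller plan. This stands in part: unweighted is an inference. But the article does not leave the topic open. It names a statistic, and that name without weights is ordinarily read as the unweighted version.
- **Consequence.** A reader might infer that good agreement would be reported as poor. The article sets no cut-off for poor agreement and bases no decision on kappa. On items the coefficient is attenuated, not near zero, and it rises with true agreement. This part stands.
- **Reach.** The article does not say that kappa is the whole of the child–parent comparison. The Limitations section lists analysis of both perceptions among its measures against recall bias, but does not mention kappa there. So it would be too strong to say that the safeguard against recall bias rests on this coefficient. Child–parent agreement is also not among the stated primary or secondary aims.

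What survives is that the only agreement statistic named does not suit ordered responses on its ordinary reading, and gives no information on systematic difference.

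**Conclusion.** The concern holds in a limited form. If the sentence in section 2.6 is followed as ordinarily read, item-level child–parent agreement is understated: about 0.25–0.5 unweighted against about 0.6–0.85 quadratic-weighted, for assumed latent correlations of 0.7 to 0.9. The sizes depend on assumed cut-points and normality; the direction held under every set tried. Near-zero values (about 0.03 at correlation 0.80 and 0.08 at 0.95, assuming SD 15 and 84 pairs) would arise only if kappa were also used on the total score, which the article does not state. The missing direction and size of a systematic child–parent difference is a real gap in the one named statistic, with or without weights.

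Severity is low. This is a descriptive comparison, and exercise capacity, fatigue, the between-group analyses and the sample size are untouched.

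**What to change.** Replace the agreement sentence in section 2.6 with one that does three things:

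1. States the unit of analysis: items, scores or both.
2. For the 0–4 items, uses weighted kappa and states the weights. Quadratic weights are a reasonable choice because the result lies close to the ICC: on the simulated total score at r = 0.8 the two were 0.79 and 0.80.
3. For the total, Physical and Psychosocial scores, uses a two-way absolute-agreement ICC with 95% CI, together with the mean child–parent difference and limits of agreement.

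The cost is one sentence and slightly more analysis work. No new data are needed, since both forms are already collected at both visits.
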